**5. Inclusion/Exclusion Criteria**

Participants must satisfy the following inclusion criteria to be considered eligible for entry into this study:

Inclusion Criteria

Chronic ischemic or hemorrhagic left hemisphere stroke

Fluent speaker of English by self-report

Age 18 or older

6 months post onset of stroke

Diagnosis of aphasia and naming impairment using the Western Aphasia Battery-Revised

Exclusion Criteria

Lesion in the right cerebellum

Previous neurological disorder (other than stroke) affecting the brain, or any other neurodegenerative disorder or psychiatric disorder

Seizures during the previous 6 months

Uncorrected visual loss or hearing loss by self-report

Use of medications that lower the seizure threshold (e.g., methylphenidate)

Use of NMDA antagonists (e.g., memantine)

>80% correct response on the Philadelphia Naming Testing at baseline

History of brain surgery or any metal in the head

Severely impaired auditory comprehension (lower than 2 on the Comprehension subscore on the WAB-R)

Severely limited verbal output (lower than 2 on the Spontaneous Speech rating scale on the WAB-R)

Individuals with severe claustrophobia, cardiac pacemakers or ferromagnetic implants, and pregnant women will be excluded from the MRI portion of the study.

**6. Drugs/Substances/Devices**

1. *The rationale for choosing the drug and dose or for choosing the device to be used.*

tDCS has been established as a valid and reliable tool for at least temporarily affecting brain and behavior with minimal risks. Stimulation will be delivered by a battery-driven constant current stimulator (Soterix device, or a comparable model). The stimulator is not connected to a mainline power source and cannot produce in excess of 4mA of current. We will use non-metallic, conductive rubber electrodes covered by saline-soaked sponges to minimize the potential for chemical reactions at the interface of the scalp or skin and the electrodes.

1. *Justification and safety information if FDA approved drugs will be administered for non-FDA approved indications or if doses or routes of administration or participant populations are changed. N/A*
2. *Justification and safety information if non-FDA approved drugs without an IND will be administered. N/A*

**7. Study Statistics**

1. *Primary outcome variable*

The primary outcome will be defined as the change in accuracy of naming measured by the Philadelphia Naming Test, one week after the end of semantic feature analysis (SFA)

1. *Secondary outcome variables*

In addition to the primary outcome, several secondary analyses will be conducted. (1) Trained Picture Naming. We will assess if tDCS has an effect on naming items trained during treatment (trained picture naming). We will assess change in trained picture naming before treatment to within 1 week after the end of treatment. Follow up testing will be done at one month, three months, and six months after the completion of the treatment. (2) Discourse. We will assess change in discourse abilities, as measured by the change in the total Content Units (CU) and syllable per CU produced by the participants during connected speech. Participants will be required to describe the Cookie Theft Picture from the Boston Diagnostic Aphasia Examination. (3) Functional Communication Skills. We will also measure changes in everyday functional communication skills assessed with the Communication Activities of Daily Living, third edition (CADL-3). (4) Finally, we will administer 3 tests from the Research Outcome Measurement in Aphasia-Core Outcome Set (ROMA-COS) at baseline, 1-week post treatment, and at 1-month, 3-month, and 6-month follow-up time points. The WAB-R will be administered as a part of the baseline testing. We will also assess changes in emotional well-being (measured by General Health Questionnaire (GHQ)-12 and quality of life (measured by Stroke and Aphasia Quality of Life Scale (SAQOL-39).

1. *Statistical plan including sample size justification and interim data analysis*

Statistical Analysis

Aim 1: Determine whether cathodal tDCS to the right cerebellum combined with evidenced-based anomia treatment improves picture naming.

Hypothesis1a: 15 sessions of cathodal tDCS over the right cerebellum + SFA treatment will be associated with greater improvement in naming untrained pictures (as measured by the change in PNT),1-week post treatment, compared to sham + SFA.

Statistical analysis**:** The analyses will follow the Intention-to-treat (iTT) principle *where participants are analyzed based on the group to which they are randomized regardless of early termination, missing data or errors in randomization detected post hoc.* The primary outcome variable will be change in accuracy of naming untrained items as measured by the PNT within 1 week after semantic feature analysis ends.

The primary hypothesis is H_0_: mu_1_ = mu_2_ versus H_A_: mu_1_ $\neq$ mu_2_, where mu_1_ is the mean change in accuracy of naming untrained items between baseline and 1-week post- semantic feature analysis in the tDCS group and mu_2_ is the mean change in accuracy of naming untrained items between baseline and 1 week post semantic feature analysis in the sham group. Average Treatment Effect (ATE) will be estimated using linear regression model with change in accuracy of naming untrained items at 1 week as the dependent variable and group assignment (real tDCS versus sham) as the independent variable. ATE is estimated by the coefficient for the group assignment.

As a secondary analysis, we will consider non-parametric mixed models for analyses of functional response over time. In particular, let Y_ijk_ = u_ik_ + fk(j) + e_ij_ where Y_ij_ is the the outcome for subject i on occasion j (0, 1, 3, 6) within treatment arm k. (Thus, both i and k are necessary to identify a subject). No covariates are necessary because of the randomization (though see Aim 2). f_k_(j) is a functional model we will estimate using quadratic regression splines with knot points at each of the time points. Given there are so few time points, we will not penalize the spline fit. A non-parametric estimate of a treatment effect is given by f_2_ – f_1,_ which can show time-specific treatment effects when evaluated at specific points j. This will also demonstrate the rate (when and if) at which TCDS effects ebb. An overall effect can be estimated by simply taking the integral of f_2_ – f_1_ (i.e. the functional averaged effect over time). A null hypothesis of zero represents no time averaged effect of the treatment. Given that we will use regression splines, every estimator reduces to standard contrasts of regression parameters, and thus can be implemented in any statistical software package.

Hypothesis 1b: For secondary outcomes, we hypothesize that cathodal cerebellar tDCS results in greater improvement in trained picture naming, greater improvement in discourse (as measured by total content units (CU) and syllable per CU in picture description) and greater improvement in functional communication skills (as measured by change in Communication Activities of Daily Living–CADL-3) compared to sham.

Statistical Analysis: We will evaluate the effect of tDCS on naming trained items, discourse and functional communication skills. In addition, we will also evaluate the effect of tDCS on WAB-R Aphasia Quotient, SAQOL, and GHQ.The analyses will follow similar approach to Aim 1a.

Aim 2: To identify whether neural (functional and structural) biomarkers and linguistic characteristics can predict response to cerebellar stimulation and SFA treatment.

Hypothesis2: Baseline resting state functional connectivity, structural connectivity, lesion volume and site, and overall aphasia severity and naming severity will predict response to cerebellar tDCS treatment.

Statistical analysis for Aim 2**:** This analysis considers moderation of treatment effects by pre-treatment baseline characteristics. The pre-treatment baseline characteristics include the following: Imaging: Structural (lesion volume, site, FA, MD), Functional (Fisher transformed connectivity values (*z* scores); Linguistic: (Aphasia Severity score as assessed by WAB-R, Naming severity score assessed by PNT). As in Hypothesis 1, we will consider both a conservative approach, using standard contrasts and median splits on the moderating variables as well as a mixed model functional approach. That is, we will split moderating measures, such as the rs-fMRI Fisher Z-transformed measures of connectivity at the median values, then will test the hypothesis that the tDCS response difference varies between the below median values and the above. A standard t-test contrast approach will be adjusted for multiplicity using Bonferroni corrections given that we will separately analyze potential treatment moderators. We will focus on most proximal post treatment outcomes as our primary test, as the power for detecting moderation will likely be the greatest where the treatment effect is strongest. Our second approach will use a fully model based approach that will be able to incorporate multiple moderators simultaneously. This will not require dichotomizing the moderating variables and it will model the relationship non-parametrically. We build on the functional mixed model approach outlined before. Consider building on our model as Y_ijk_ = u_ik_ + x_i_ B + f_k_(j, x_i_) + e_ij_ where here x_i_ is a vector of pretreatment characteristics of interest, such as a collection of lesion volumes or inter-regional Fisher Z-transformed connectivity, i is subject, k is treatment status and j is sampling occasion (time), f_k_(j, x_i_) is the non-parametric interaction effect between treatment status and the potential interaction moderating variables. Note that the function f_k_(j, x_i_) is now a function of both time and baseline participant characteristics. Therefore, we will follow our testing strategy as before. However, of interest is whether f_2_ – f_1_ is flat with respect to dependence on xi. Specifically, consider the simpler model where Y_ijk_ = u_ik_ + x_i_ B + q_k_(j) + e_ij_ where note that the treatment effect, represented by q_k_(j) in the simpler model, does not depend on the moderating variables. Testing between the more complex and simpler models is a test of whether the treatment effect is influenced by the moderating variables. Inference will be performed via the bootstrap. Of note, flatness f_2_ – f_1_ with respect to the moderating variables is a strong null. We will also consider a weaker null under linear separability: f_2_(j, x_i_) = g_k_(j) + h_k_(x_i_). Here the non-parametric treatment function allows for a non-linear effect of the potential moderating variables where they do not have any actual interaction with the treatment effect. While this overall approach is complex, it offers a complete picture of treatment response over time and the impact that moderating variables have. In addition, the model allows us to fit much more complex potential relationships between the impact of treatment and the moderating variables and allows us to consider the moderating variables simultaneously. To summarize the approaches, we will proceed in this order

1. T-test comparing the treatment effect across median splits of the moderating variables performed separately, one at a time.
2. A non-parametric modeling approach using spline based linear models testing whether the potential moderating variables interact with the treatment effect over time. We will consider two variations of this approach:
   1. One that assumes linearity
   2. One that assumes non-parametric functions

Sample Size Determination

We used the data from the PI’s K99 study (crossover trial) to estimate the variability of untrained naming score. 52 participants (26 per group) will give us 80% statistical power to detect 0.7 SD difference in change in accuracy of naming untrained items at 1-week post treatment between the study arms. This was done using Wald test for group assignment coefficient in linear regression at 0.1 level of statistical significance. The effect size (0.7SD) is a bit conservative compared to the difference observed on group comparison for 21 participants (10 in tDCS and 11 in sham) in the K99 data, when the tDCS was administered in Phase 1. We propose to enroll 60 participants to account for 10% attrition.

Missing Data

*The analyses will follow the Intention-to-treat (iTT) principle where participants are analyzed based on the group to which they are randomized regardless of early termination, missing data or errors in randomization detected post hoc. To minimize possible biases, analyses will be by intention to treat; any missing data will be addressed with the technique of multiple imputation (Ball et al., 2002; Rubin, 2009), generally recognized as best for handling missing data (Little et al., 2012).*

1. *Early stopping rules. N/A*

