**4. Study Procedures**

1. *Study design, including the sequence and timing of study procedures*

*(distinguish research procedures from those that are part of routine care).*

Study Procedures Overview

This study, Cerebellar Stimulation for Aphasia Rehabilitation (CeSAR), is a Phase II trial of cathodal cerebellar tDCS plus anomia (SFA) treatment vs. sham plus anomia (SFA) treatment, evaluated in double-blind, randomized, sham-controlled design in chronic stroke. Participants with aphasia will be enrolled at 2 sites within the Johns Hopkins Rehabilitation Network at least 6 months after the onset of stroke. The two sites will be the Johns Hopkins Hospital and Howard County General Hospital. Participants will undergo language testing and MRI to determine eligibility and then will be randomly assigned to cerebellar tDCS plus anomia treatment or sham plus anomia treatment. Participants will receive 15 sessions of anomia treatment (3-5 sessions per week), as in the ongoing K99/R00 study. Participants will be evaluated prior to the start of treatment, one-week post treatment, 1, 3, and 6-months post- treatment on primary and secondary outcome variables.

Participants will be randomized 1:1 (cathodal tDCS or sham tDCS), stratified by site (JHH vs Howard County), aphasia type (fluent vs. non-fluent, classified using WAB-R), and severity (classified using WAB-R Aphasia Quotient in 4 categories (very severe aphasia: 0–25, severe aphasia: 26–50, moderate aphasia: 51–75, and mild aphasia: 76-93.8). All participants, the members of the study team who administered the assessments and treatments as well as the study biostatistician performing the statistical analyses will be blinded.

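### The secondary longitudinal model lists four occasions for five scheduled assessments, defines neither occasion 0 nor the scale of Y, and makes no use of baseline as an adjustment

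*Protocol*

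**What the plan says.** Protocol section 4 (Study Procedures Overview) has participants "evaluated prior to the start of treatment, one-week post treatment, 1, 3, and 6-months post- treatment". The visit list in the same section repeats this, and section 7 names the same five time points for the core-outcome-set tests.

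The primary analysis in section 7 is a linear regression of change on arm: "The primary outcome variable will be change in accuracy of naming untrained items as measured by the PNT within 1 week" of the end of therapy.

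The secondary longitudinal analysis that follows sets Y equal to a subject effect, an arm-specific curve f and error, where Y is the "outcome for subject i on occasion j (0, 1, 3, 6) within treatment arm k". On adjustment it says: "No covariates are necessary because of the randomization (though see Aim 2"). The curves are "quadratic regression splines with knot points at each of the time points". The treatment effect is f2 − f1, "which can show time-specific treatment effects when evaluated at specific points j", and "An overall effect can be estimated by simply taking the integral of f_2_ – f_1" over time. The text does not say which visit is occasion 0, or whether Y is a score or a change in score.

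**The concern.** Four occasions cannot be matched to five assessments without saying which one is left out or used in another way. The choice decides what f2 − f1 means. Nothing in the formula subtracts or conditions on baseline, so unless Y is already a change score the contrast is a difference in mean scores, whereas the primary hypothesis concerns a difference in mean change.

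This model is the stated means of showing when a tDCS effect fades. It also has reach: section 7 gives the other secondary outcomes an approach similar to that of Aim 1a, and the Aim 2 moderator model is built on it. An imprecise longitudinal result, or one measuring a different quantity from the primary test, would be hard to read beside it.

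**Working it through.** **Inputs from the protocol.** Section 4: five assessments. Section 7: model occasions 0, 1, 3, 6; no covariates; effect f2 − f1 and its integral. Sample Size Determination: 26 per arm, 0.7 SD of change, 80% power, level 0.1. The primary hypothesis is two-sided.

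**Assumption.** Equal variances over time and a correlation ρ between baseline and follow-up PNT score. The protocol gives no ρ, so a range is shown.

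**Step 1: the plan's own figure.** n per arm = 2(1.645 + 0.842)²/0.7² = 25.2, rounded up to 26. Noncentral-t power at 26 per arm is 80.1%. The stated design reproduces.

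**Step 2: the possible readings.**

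| Y | Occasion 0 | Consequence |
|---|---|---|
| level | baseline | 1-week visit absent; f2(0) − f1(0) is a pre-treatment gap |
| level | 1 week | baseline not used; f2 − f1 is a difference in levels |
| change | baseline | Y is zero for everyone at occasion 0; 1-week visit absent |
| change | 1 week | all five assessments used; f2 − f1 is the difference in change |

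**Step 3: weight of baseline in the overall effect, if 0 is baseline.** By the trapezoid rule over 0 to 6, the weight on occasion 0 is (1/2)/6 = 1/12. The weights at 1, 3 and 6 are 1/4, 5/12 and 1/4.

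**Step 4: precision at one visit.** Take the SD of change as 1.

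- SD of the level: s = 1/√(2(1 − ρ)).
- SD after baseline adjustment: s√(1 − ρ²).
- Standard error of a between-arm difference: SD × √(2/26) = SD × 0.277.
- Power: noncentral t, two-sided 0.10, effect 0.7. The adjusted analysis loses one degree of freedom.

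| ρ | SE, change | SE, level | SE, adjusted | Power, change | Power, level | Power, adjusted |
|---|---|---|---|---|---|---|
| 0.5 | 0.277 | 0.277 | 0.240 | 80% | 80% | 89% |
| 0.7 | 0.277 | 0.358 | 0.256 | 80% | 61% | 85% |
| 0.8 | 0.277 | 0.439 | 0.263 | 80% | 47% | 84% |
| 0.9 | 0.277 | 0.620 | 0.270 | 80% | 30% | 82% |

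The normal approximation gives figures up to about one point higher (83–90% for the adjusted analysis).

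**Step 5: bias or imprecision?** In simulated trials with no treatment effect and a random subject intercept, the mean level difference at month 1 was about 0, so there is no systematic bias. Its correlation with the baseline difference was 0.70 at ρ = 0.7 and 0.90 at ρ = 0.9, so the random intercept does not remove a chance imbalance between arms. A baseline difference of one standard error shifts the later level contrast by ρ × SE(level): 0.7 × 0.358 = 0.25 SD of change at ρ = 0.7, and 0.9 × 0.620 = 0.56 at ρ = 0.9.

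**The case against.** A reader might infer that Y must be a level, so that the model necessarily drops a visit and measures something other than the primary hypothesis. The protocol does not support this. It calls Y only the outcome, and just before the model it defines the primary outcome as a change. The clock of 1, 3 and 6 months after treatment, and the aim of tracking how effects fade, fit a model that starts at the 1-week visit. On that reading nothing is dropped.

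A reader might also infer bias. That does not follow either: randomisation keeps the post-treatment level contrast unbiased, so the protocol's reason for omitting covariates is sound as to validity. Minimisation on site, aphasia type and severity category should restrain imbalance further.

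The power loss needs both a level outcome and a correlation above 0.5. It describes a single-visit comparison, not the full mixed model, and the protocol claims no power for this analysis. Excluding people above 80% correct at baseline may also lower the correlation. If 0 is baseline, a difference in change could be formed as a contrast of the same fit.

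These points stand and limit the finding. They do not remove it: the favourable reading is nowhere stated, and the effect is written as f2 − f1 with no baseline contrast. Aim 2 does admit baseline characteristics, including naming severity, but that does not adjust the Aim 1 model. Visit coding can be left to a statistical analysis plan, but here the protocol itself gives an occasion list that does not match its schedule.

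**Conclusion.** The mismatch of four occasions with five assessments, the undefined occasion 0 and scale of Y, and the absence of any baseline term are firm. Their consequence is conditional. Only with Y as change and 0 as the 1-week visit does the model use every assessment and match the primary estimand, and even then it forgoes the gain from a baseline covariate (standard error 0.277 against 0.240–0.270). On levels the cost is precision and a shift from chance imbalance: nothing at a correlation of 0.5, rising to a fall from about 80% to 30% power at 0.9, with the correlation assumed. If 0 is baseline, about 1/12 of the overall effect is a pre-treatment difference.

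The primary analysis is a separate regression on change at 1 week and is unaffected. This is therefore not a must-fix; it is a worthwhile correction that needs no new data.

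**What to change.** State how the model's occasions map to all five assessments and what scale Y is on. Then use one of two forms:

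1. Model change from baseline at the four post-treatment visits (1 week, 1, 3 and 6 months) with the baseline score as covariate.
2. Model the score at all five assessments with one common baseline mean for both arms.

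Define the effect at each visit as the between-arm difference in baseline-adjusted change, and take the time-average over post-treatment visits only.

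One related detail should be settled in the same edit. A quadratic spline with interior knots at the time points has five parameters per arm on four distinct times, or six on five, so an unpenalised fit is not identified, and adding the missing visit does not cure this. A separate mean per visit and arm, with stated weights for the time-average, avoids the problem.

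The cost is a rewording of the secondary model. All the data are already scheduled for collection.

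### The overall effect in the secondary longitudinal analysis (the integral of f2 − f1) is not estimable, because the unpenalised quadratic spline has at least one more parameter per arm than there are visits

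*Protocol*

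**What the plan says.** Section 7 of the protocol (Study Statistics, statistical analysis for Aim 1) adds to the primary 1-week regression a secondary mixed model over time. Its response is "the outcome for subject i on occasion j (0, 1, 3, 6) within treatment arm k", written as a subject term plus an arm-specific function of time plus error. No covariates enter this model.

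The time function is one the plan will "estimate using quadratic regression splines with knot points at each of the time points". On smoothing it says: "Given there are so few time points, we will not penalize the spline fit". Differences between the two arm curves at given times are the time-specific effects. For the summary, "An overall effect can be estimated by simply taking the integral of" the difference between the curves, and a null value of zero for that summary means no time-averaged effect. The paragraph closes by claiming that "every estimator reduces to standard contrasts of regression parameters, and thus can be implemented in any statistical software package".

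Section 4 (Study Procedures) gives a longer schedule than the four occasions in the model: "Participants will be evaluated prior to the start of treatment, one-week post treatment, 1, 3, and 6-months post- treatment". That is five assessments, and section 7 does not say whether occasion 0 is baseline or the 1-week visit.

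**The concern.** Visits at m fixed times determine m means per arm and nothing more about the shape of the curve. A quadratic spline with a knot at every visit asks for more than that, and the plan excludes a penalty without reducing the basis. Many curves then pass through the same fitted visit means and differ only between visits. Any quantity that uses the curve between visits, as an integral does, takes a different value for each of them.

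The time-averaged effect is the plan's single summary of the treatment effect over follow-up, with its own null hypothesis. If it is not determined by the model, the reported estimate depends on which redundant column the software drops, a choice the protocol does not fix.

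**Working it through.** The plan gives no figure on this point to reproduce. Its one computable figure is the sample size, which does reproduce: 2 × (1.645 + 0.842)² / 0.7² = 25.2, so 26 per arm. It plays no part below.

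**Inputs.** From section 7: degree 2, knots at each time point, no penalty, occasions 0, 1, 3, 6. From section 4: five assessments. Assumed: the profiles of arm differences, and the time coding for five visits.

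**1. Parameters against visits.** A quadratic spline has 3 columns (1, t, t²) plus one column (t − κ)₊² per knot κ. With m visits and only the m − 2 interior knots counted, that is 3 + (m − 2) = m + 1 parameters for m means.

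| Reading | Columns | Rank |
|---|---|---|
| 4 occasions, knots at 1 and 3 | 5 | 4 |
| 4 occasions, knots at all four times | 7 | 4 |
| 5 occasions, interior knots | 6 | 5 |
| 5 occasions, knots at all five times | 8 | 5 |

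A B-spline basis gives the same result (4 × 5, rank 4; 5 × 6, rank 5). The remaining steps use the most favourable reading, interior knots only.

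**2. The undetermined direction.** For occasions 0, 1, 3, 6 take

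s(t) = −t + t² − 1.5(t − 1)₊² + (5/6)(t − 3)₊².

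Then s(0) = 0; s(1) = −1 + 1 = 0; s(3) = −3 + 9 − 6 = 0; s(6) = −6 + 36 − 37.5 + 7.5 = 0. Any multiple c·s can be added to an arm's curve without changing a fitted value at any visit.

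**3. Its integral.** Over 0 to 6: −18 + 72 − 62.5 + 7.5 = −1. This is not zero, so adding c·s moves the time average by −c/6, and the integral is not estimable. Equivalently, appending the integral vector to the design matrix raises its rank from 4 to 5.

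In general, with visit intervals h₁, h₂, …, the integral is −(h₁/6)(h₁² − h₂² + h₃² − …). For five visits coded 0, 0.25, 1, 3, 6 months, the bracket is 0.0625 − 0.5625 + 4 − 9 = −5.5, again not zero. Two codings that add a treatment period before the 1-week visit also leave the integral non-estimable.

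**4. Size, assumed differences 0, 0.7, 0.5, 0.2 SD.** One exact solution is 1.5t − 0.8t² + 0.8(t − 1)₊², with integral 27 − 57.6 + 33.33 = 2.733. Adding c·s gives coefficients 1.5 − c, −0.8 + c, 0.8 − 1.5c and 5c/6, and time average (2.733 − c)/6. Dropping a column means choosing c so that its coefficient is zero:

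| Column dropped | c | Time average (SD) |
|---|---|---|
| t | 1.5 | 0.206 |
| t² | 0.8 | 0.322 |
| (t − 1)₊² | 0.533 | 0.367 |
| (t − 3)₊² | 0 | 0.456 |

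All four fit the visits exactly. The ratio of largest to smallest is 0.456/0.206 = 2.2. The trapezoid rule gives (0.35 + 1.2 + 1.05)/6 = 0.433.

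**5. Size, assumed differences 0.7, 0.6, 0.4, 0.2 SD.** One solution is 0.7 − 0.0867t − 0.0133t² + 0.02(t − 1)₊², with integral 2.513. The same four drops give c = −0.0867, 0.0133, 0.0133 and 0, and averages 0.433, 0.417, 0.417 and 0.419, a spread of about 4%. The trapezoid rule gives (0.65 + 1.0 + 0.9)/6 = 0.425.

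**6. Size, constant 0.7 SD.** The solution is the intercept alone, so c = 0 for every drop and the average is 0.700 each time.

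**7. The spread also depends on the basis.** If a column of the five-column B-spline basis is dropped instead, the profile in step 5 gives 0.20 to 0.50. The small spread there belongs to the truncated-power columns and is not a bound.

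**8. What restores estimability.** A linear spline with knots at the interior visits, or a quadratic spline with one fewer interior knot, has 4 parameters for 4 visits (5 for 5), full rank and an estimable integral.

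**The case against.** The best case for the plan is that little depends on this. It is a secondary analysis the plan says it will consider. The model is saturated at the visits, so fitted visit means, visit-specific arm differences and the likelihood are unique. Basis coding is often settled in a statistical analysis plan, and one may exist. All of that stands and limits the severity. It does not remove the point: the protocol itself states the degree, the knots, the absence of a penalty and the integral, and following those statements gives no unique overall effect.

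Actual assessment dates might make the matrix full rank. But the protocol indexes time by nominal occasion, and identification would then rest only on scatter around the visit dates. More participants or the subject term do not help, because the deficiency is in the fixed-effect time basis.

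A reader might infer several stronger things that the documents do not support:

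- *That the whole model fails.* Only the curve between visits and its integral are lost.
- *That a penalty is the only remedy.* A smaller basis also works (step 8).
- *That the overall test has inflated type I error.* If the arms have equal means at every visit, each fixed choice of dropped column is a linear contrast of visit differences with expectation zero. What is left open is the weighting in the estimand.
- *That Aim 2 is invalid.* Its model-based tests compare a larger with a simpler model, its first-listed approach is median-split t-tests, and the integral is not its stated test. No stated Aim 2 test has been shown to change.
- *That the ambiguity is always about twofold.* That figure belongs to one assumed profile and treats occasion 0 as a pre-treatment visit with no arm difference, which section 7 does not say.

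**Conclusion.** The point holds for the integral and for the curve between visits. As specified, the spline has at least one more parameter per arm than there are visits, under either the four occasions in the model or the five in the schedule. The planned overall effect is therefore not estimable, and the sentence on standard contrasts is wrong for it. This rests on nominal visit times, as the protocol indexes them, and on no constraint beyond those stated.

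The algebra is certain; the practical size is not. Under the four truncated-power drops the range runs from no spread (constant difference) through about 4% (steady decline) to 2.2-fold (a rise from zero followed by decline). All three profiles are assumptions. The primary 1-week analysis and the sample size are unaffected. This should be fixed before analysis, as a correction to a secondary analysis.

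**What to change.** Replace the spline sentence with a time basis that has no more parameters than visits: visit as a categorical factor within arm, or equivalently a linear spline with knots at the interior visits. A quadratic spline with one fewer interior knot is also full rank if a smoother curve is wanted, but the knot to omit must then be named.

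Define the overall effect as a pre-specified contrast of the visit-specific arm differences. Trapezoid weights are one choice: for occasions 0, 1, 3, 6 they are 0.5/6, 1.5/6, 2.5/6 and 1.5/6. The sentence on standard contrasts then becomes true.

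In the same edit, state which assessments enter the model and what occasion 0 is, because the weights depend on it. The same time basis may be used in Aim 2 for consistency.

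The cost is a wording change. Standard mixed-model software fits the result, and no data collection or sample size changes.
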